#### MRI/^1^H-MRS

MRI images will be scored according to the Kidokoro assessment tool (Kidokoro et al., 2013). Briefly, cerebral white matter, cortical gray matter, deep gray matter, and cerebellar abnormalities will be independently graded, and then the scores combined to calculate a single global brain injury score. The assessor will also note the presence of hemorrhage or cystic lesions throughout the brain. Hemorrhagic lesions will be graded using the Papile classification system (Papile et al., 1978) and cystic lesions characterized as periventricular leukomalacia, periventricular hemorrhagic infarction, or other (Barkovich, 2000).

Metabolic ratios from ^1^H-MRS spectra obtained with a TE of 135 ms will be calculated as previously described, with water used as an internal reference to normalize metabolite signal intensities (Koob et al., 2016).

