#### Neurodevelopmental Observations

Motor function will be assessed by a developmental therapist trained in GMA and blinded to the clinical history of the infant. At term CPA, infants will be assessed on withering movements, which should include complex movements of the arms, legs, neck, and trunk. Poor withering movements include rigid or chaotic movements that lack fluency and coordination (Spittle et al., 2013) and are predictive of adverse neurodevelopmental outcomes. At 3 months of CPA, infants will be assessed on fidgety movements, which appear as small continual movements of limbs in all directions. Poor quality fidgety movements include larger amplitude and jerking movements (Spittle et al., 2013) and are again predictive of later outcomes. Infants will be scored independently at each postnatal age.

At 3-month CPA, infants’ development will also be reviewed using the DAYC-2 assessment tool (Saleh and Smadi, 2017). An overall score from the five domains tested (cognition, communication, social-emotional development, physical development, and adaptive behavior) will be generated for each infant. Collectively, MRI, GMA, and DAYC-2 scores will be used to assess the potential risk of poor neurological outcomes, based on early diagnosis strategies for cerebral palsy (Novak et al., 2017).

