### Statistical Analysis

Characteristics of the population will be tabulated, along with appropriate descriptive statistics of the study sample. Continuous data will be assessed for normality and expressed as means and standard deviations or median and interquartile range as appropriate. Categorical data will be expressed as counts and proportions. Average creatine content from nutrition per week for each baby in the early postnatal period will be calculated.

Differences in creatine and GAA measures (^1^H-MRS, plasma or urine) between infants born preterm and those born at term will be assessed at CPA using a t-test or Mann-Whitney U test as appropriate. The correlation between gestational age at birth and creatine and GAA measures at CPA will also be determined using a Spearman or Pearson correlation. Preterm infant plasma and urine creatine and GAA concentrations and creatine:GAA ratio in the early postnatal period will be described and plotted. Associations between cerebral creatine content, plasma and urine creatine concentrations with maternal, and infant characteristics at CPA will be determined using Spearman or Pearson correlations for continuous data (maternal age, gestational age, birth weight, parity, gravity, placental weight) or a t-test or Mann-Whitney U test for categorical data (infant sex, mode of delivery, maternal comorbidities, country of birth, ethnicity, and dietary preferences), as appropriate. Differences in creatine, GAA, and amino acid content of nutrition sources (TNP, formula or breast milk) will be determined using a one-way ANOVA or Kruskal-Wallis H test as appropriate. The association between creatine, GAA, and amino acid content of nutrition sources (TNP, formula or breast milk) and infant plasma and urine creatine at CPA will be assessed using a Spearman or Pearson correlation as appropriate. Finally, the association between cerebral creatine content, plasma creatine levels, and the ratio of plasma:cerebral creatine at CPA with GMA, MRI global injury, and DAYC-2 scores will be determined using linear regression at both CPA and at 3 months’ corrected postnatal age. Potential confounders such as gestational age and maternal and infant characteristics will be assessed, along with collinearity, prior to performing multivariable linear regression.

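### Linear regression is the only model named for the general movements assessment (GMA), which the protocol describes as a judgement of movement quality with no numeric scale

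*Protocol article*

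**What the plan says.** The last part of the Statistical Analysis section of the protocol article relates cerebral creatine, plasma creatine and their ratio to three neurological measures, and states that associations "with GMA, MRI global injury, and DAYC-2 scores will be determined using linear regression". Gestational age and the maternal and infant characteristics are potential confounders that "will be assessed, along with collinearity, prior to performing multivariable linear regression". Both steps use a linear model and neither has an alternative. Every other inferential comparison in that section has a rank-based fallback.

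The three measures differ in kind:

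- **GMA.** Neurodevelopmental Observations (under Sample and Data Analysis) describes it by quality of movement. At term, "Poor withering movements include rigid or chaotic movements that lack fluency and coordination". At 3 months, "Poor quality fidgety movements include larger amplitude and jerking movements". It adds that "Infants will be scored independently at each postnatal age". No levels, range or scoring rule are given, although Secondary Outcome Measures calls it a score.
- **MRI.** Four brain regions are graded, and "the scores combined to calculate a single global brain injury score".
- **DAYC-2.** One overall score is formed from five domains.

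**The concern.** One model is applied to three unlike outcomes. As described, the GMA sorts infants by whether their movements look as expected or poor, and a different movement pattern is judged at each age. That suggests a binary or ordered category. A slope on category codes depends on how the codes are chosen. If the codes are 0 and 1, the fitted line can leave the range of a probability, and the residual variance p(1 − p) changes along the line, so the usual standard error is not right when an association exists.

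This matters because the Discussion intends the data to supply effect sizes for future studies and possibly a randomised trial. The estimate and its interval will therefore be used, as well as the p-value.

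Confounding is a second, related matter. The Introduction says neurodevelopmental risk rises as gestational age falls and hypothesises lower creatine in preterm infants, and Recruitment is by gestational-age band. By the protocol's own reasoning, gestational age is the main confounder of any creatine–outcome association. The text does not commit to keeping it in the adjusted models.

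**Working it through.** The plan gives no figure for these regressions, so there is none to reproduce. The check asks how badly ordinary least squares behaves on outcomes of these types at this study's size.

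**Inputs from the article.** Five groups of 20 give 100 infants (Recruitment). Sample Size cites a 20–25% failure rate for MRI/MRS and a possible 20% loss at 3 months. Taking 20% for each:

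- term analyses: 100 × 0.8 = 80
- 3-month analyses: 100 × 0.8 × 0.8 = 64

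**Assumptions (not in the article).** One standardised continuous exposure; two-sided 5% test; 3000 runs per setting. Outcomes:

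- binary GMA, 10% or 30% abnormal at average exposure, log-odds slope 0, −0.7 or −1.4 per SD
- three-level GMA with the same slopes
- right-skewed summed score (negative binomial, mean 4 at average exposure), log-mean slope 0, −0.2 or −0.4 per SD

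The measure of error is the mean model standard error divided by the empirical SD of the slope. A value of 1 is correct.

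**No association.** Rejection was 4.0% to 5.6% for binary or three-level GMA and 4.6% to 5.4% for the summed score. The SE ratio was 0.97 to 1.04.

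**Association present.**

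| Outcome | SE ratio | Fitted values outside 0–1 |
|---|---|---|
| Binary GMA | 0.92 to 1.18 | 2% to 14% |
| Three-level GMA | 1.01 to 1.09 | not applicable |
| Summed score, moderate slope | 0.92 to 0.93 | not applicable |
| Summed score, strong slope | 0.79 to 0.80 | not applicable |

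The extremes for binary GMA, both at n = 64 and slope −1.4:

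- 10% abnormal: 0.0423 / 0.0460 = 0.92 (standard error 8% too small)
- 30% abnormal: 0.0528 / 0.0447 = 1.18 (18% too large)

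For the summed score at n = 80 with the strong slope, 0.4404 / 0.5490 = 0.80, or 20% too small.

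**Robust (HC3) standard errors.** In that last setting, 0.5334 / 0.5490 = 0.97, so most of the error is repaired. HC3 rejection under no association was 2.1% to 6.0% over all settings. The 2.1% came from the rarest binary outcome at n = 64, where the test is conservative.

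**Why the variance is unequal.** If abnormal GMA ran from 5% to 50% across groups (assumed), p(1 − p) would go from 0.05 × 0.95 = 0.0475 to 0.5 × 0.5 = 0.25, a ratio of 5.3. From 10% to 40% it would go from 0.09 to 0.24, a ratio of 2.7. These ratios show the mechanism. They are not the error in the slope's standard error, which is the much smaller figure in the table.

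**Number of events.** At an assumed 10% abnormal, 80 infants give 8 events and 64 give about 6 (0.10 × 64 = 6.4). Ordinary logistic regression with several covariates would be unstable at that number, hence the penalised version in the fix.

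**The case against.** A reader might infer that the GMA and MRI estimates and standard errors would be invalid and that the whole neurological aim fails. The documents and the check do not support that:

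- The article calls the GMA a score and never says it is categorical. It is condensed, and coding may be set out in a fuller document. This stands. The point is therefore conditional on categories being recorded, and rests on the model that the article does fix.
- The MRI global score is a multi-level sum. Linear regression on such a score is common and defensible, and nothing in the article shows that it piles up at low values. This stands. Skew would call for residual checks or robust errors, not a different model.
- A linear fit to a 0/1 outcome estimates an approximate risk difference, and its test under no association is near nominal. This stands against the word invalid. It does not make the slope a good effect size to carry into a later trial.
- The dependent variable is not stated. If creatine were the outcome, GMA category could be a legitimate predictor. This stands only in part: the neurological measures are listed as outcomes, and the hypothesis runs from low creatine to dysfunction.
- One might also infer that the collinearity check would remove gestational age. No removal rule is stated, so this is a risk and not a stated plan.

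The DAYC-2, one of the three measures in the aim, is not affected.

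**Conclusion.** The point holds in limited form. The article fixes a linear model, with no alternative, for a measure that it describes only as a quality judgement. If GMA is recorded as categories, the slope is a poor effect measure, with some impossible fitted probabilities and somewhat wrong standard errors when an association exists. The test of no association is largely preserved.

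The sizes rest on assumed outcome frequencies and slopes, a single exposure without covariates, and 64 or 80 analysable infants. The largest standard-error discrepancy, about 20%, arose for the skewed summed score under a strong association and was mostly repaired by HC3.

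These are secondary outcomes in a study that calls itself mainly descriptive, and no primary outcome is touched. This is a should-fix, not a must-fix.

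**What to change.** Amend the regression text in the Statistical Analysis section to say:

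1. The neurological measure is the dependent variable and the creatine measure the exposure.
2. The GMA scale is stated, and GMA at term and at 3 months is analysed separately. If it is recorded as expected versus poor, use logistic regression, Firth-penalised if events are few. If ordered categories are used, use proportional-odds regression.
3. Linear regression is kept for the DAYC-2 and for the summed MRI global score. For the MRI score, add residual checks or HC3 standard errors.
4. Gestational age at birth stays in every adjusted creatine–outcome model, whatever the collinearity check shows.

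The cost is a change of analysis wording only, with no new data. The price in precision is real: odds ratios from so few events will have wide intervals, and so will creatine slopes adjusted for gestational age if the two are strongly correlated. Those wide intervals should be reported as they are, since they show how much the data can say about creatine apart from gestational age.

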## Discussion

Both creatine and the creatine kinase circuit are critical for brain metabolism (Braissant et al., 2011). It is hypothesized that preterm infants will become creatine deplete in the early postnatal period, due to premature delivery from a maternal source of creatine *in utero,* limited capacity for endogenous synthesis postnatally, and a limited supply of creatine in newborn nutrition. This creatine depletion may alter cerebral creatine metabolism, contributing to or compounding the risk of neurological disability in this population.

We anticipate that preterm babies will have altered creatine homeostasis and reduced creatine accretion in the early postnatal period compared to an infant of the same postconceptional age. Whether or not relative creatine deficiency is associated with neurological deficit will be a secondary outcome of this study. As the results are mainly descriptive and a formal power calculation could not be completed, there is the possibility that sample size may become a limitation for some of the proposed analyses in this observational study. However, the data obtained will enable calculation of effect size for future studies. If our overall hypothesis is supported, this observational study will inform a future randomized control trial of infant dietary creatine supplementation following premature birth, with the aim of improving brain metabolism during a key stage of development and thereby reducing the burden of neurodevelopmental disability in this high-risk population.
